###### **6.11. Study Discontinuation**

In the event that the study is discontinued, subjects who have completed or who are still enrolled in the study will be notified. Any new information gained during the course of the study that might affect subjects’ safety or willingness to continue participation in the study will be communicated to participants by the study coordinator within 2 days after the principal investigator learns this information.

###### **6.12. Dissemination Policy**

###### **6.12.1. Trial Results**

The results of this trial will be published in peer-reviewed journals and presented at scientific conferences/meetings.

###### **6.12.2. Authorship**

To be eligible for authorship on any resultant publications, all potential contributors must fulfill all criteria as set forth by the International Committee of Medical Journal Editors.

###### **6.13. Declaration of Interests**

[name] is supported by an Academic Scholar Award from the University of Toronto Department of Psychiatry and has received research support from the Canadian Institutes of Health Research, Brain & Behaviour Foundation, Ministry of Health Innovations Funds, Royal College of Physicians and Surgeons of Canada, Department of National Defence (Canada) and an investigator-initiated trials from Roche Canada.

###### **7. Statistics**

###### **7.1. General Procedures and Statistical Methods**

Feasibility outcomes will be reported with descriptive statistics (i.e., counts and proportions). A minimum of 2-3 participants per month (at our single site) will be considered a sufficient recruitment rate to indicate the feasibility of a future larger multi-site trial. We will estimate the proportions of participants adherent with the protocol, that withdraw, and for data completion with a 95% CI. A full trial with this design will be deemed feasible if the lower 95% confidence limit for the rates of adherence and data completion are **≥** 80%, and if the upper limit of 95% confidence interval for the withdrawal rate is ≤ 20%. Frequencies and proportions of AEs and serious AEs will be tabulated for the total sample for each AE type. For continuous outcomes, we will report the means and standard deviations of the score and its change from baseline until the end of treatment and over the follow-up visits. We will estimate the standard deviation of PTSD severity [CAPS-5] and its within person correlation between the baseline and the end of treatment scores. The study will examine the effect size associated with psilocybin-assisted CPT in participants with PTSD, including the durability of effects on PTSD symptoms. The main analysis will be a comparison of PTSD symptoms before and after treatment. There will be analyses of changes in symptoms of depression, psychological functioning, sleep quality and PTSD severity. In week 2, the primary endpoint assessment will take place for all subjects. An independent rater not involved in therapy will administer or collect some outcome measures, and others will be based on subjects’ self-report. Baseline will be compared to the primary end point and follow up time points. This study will provide data on the impact of psilocybin in conjunction with massed CPT. Based on the outcomes, this study will primarily detect effects due to psilocybin-assisted CPT on PTSD symptoms through calculating effect sizes and significance testing. A Wilcoxon signed rank test comparing Clinician-Administered PTSD Scale for DSM-5 (CAPS-5) scores from the baseline to the primary endpoint will be the main analysis. Durability of effects will be examined by comparing changes from baseline to the assessments at 1 until 12 weeks after the final CPT session (day 7) for each PTSD subject using Friedman test, which is a non-parametric test method for repeated measures. Effects on depression symptoms, psychological functioning, trauma-related beliefs and sleep quality will also be assessed for exploratory purposes. Changes in these measures will be compared from baseline to primary endpoint for participants using Wilcoxon signed rank tests. Analyses will examine changes from baseline up to week 13 using Friedman tests. Effect sizes for the psilocybin-assisted CPT will be calculated at the primary endpoint and follow-up time points.

Passive data is effective at identifying behaviors and trends in activity but is poor in measuring people's internal states, motivation, and attitude, whereas active data is the opposite. Developing a methodology for integrating the two data sources can mitigate their respective weaknesses. The passive data capturing activity, sleep and physiological data collected by the Oura Ring will be correlated and fused with the active data collected by the clinical data. The motivation to fuse active and passive data includes the cross-validation and improvement of measurements, the explanation of human behavior, and novel opportunities to improve representative models in experimental settings. Techniques such as feature extraction, dimension reduction, feature relevance estimation for ranking, statistical analysis, and data fusion will be used on the passive and active.

The active data will serve as a ground truth to validate the passive data from the wearable device for monitoring anxiety and depression. We will use generalized machine learning models to detect and predict distress among participants and develop personalized time series machine learning models for personalized application. This will involve creating predictive models based on a participant's data and implementing the model suited for the participant. This proposal will be an iterative process. To mitigate missing data, suitable filtering and encoders may be used to interpolate and predict the expected data accordingly.

During the analysis, we will extract features from the passive physiological data for better representation. Trends, classifications, and relationships will be determined using different machine learning techniques. Implementations of pre-processing, feature extraction and machine learning will be conducted in a numerical program for efficient and powerful processing that will achieve impactful results.

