# **Study Summary**

| Name of Sponsor-Investigator:  [name], St. Michael’s Hospital | |
| --- | --- |
| Name of Investigational Product:  Psilocybin | Protocol Identification Code:  23-230 |

**ClinicalTrials.gov Number**: Not yet assigned

**Clinical Phase**: 2

| Title | Psilocybin-Assisted Massed Cognitive Processing Therapy for Chronic Posttraumatic Stress Disorder: An Open-label Trial |
| --- | --- |
| Sources of monetary or material support | Internal sources of funding |
| Brief title | Psilocybin-assisted CPT for PTSD |
| Indication: | Adults with Chronic Posttraumatic Stress Disorder (PTSD) |
| Condition(s) or focus of study | Posttraumatic Stress Disorder |
| Number of participants | 15 |
| Primary outcome | To determine the feasibility and tolerability of psilocybin-assisted cognitive processing therapy (CPT) in adults with chronic PTSD (i.e., recruitment rate, withdrawals, data completion, adherence, and number and nature of adverse events). |
| Secondary outcomes | 1. To examine the effect of psilocybin-assisted CPT on clinician-rated PTSD symptoms, self-reported treatment outcomes (e.g., depression and anxiety severity, psychological functioning, sleep quality) and putative mechanisms of change. |
| Exploratory outcomes | 1. To evaluate the effect of psilocybin-assisted CPT on digital physiological passive data collected through the use of a wearable device (Oura Ring). 2. To create a personal digital phenotype profile (pDPP) based on the wearable’s and clinical assessments’ data. |
| Safety outcome | 1. To evaluate the safety of psilocybin-assisted CPT in adults with chronic PTSD. |
| Study design | Study type: Open-label  Allocation: N/A  Intervention model: Single arm  Primary outcome: Feasibility  Phase: 2 |
| Masking | N/A |
| Date of enrollment | Start date: Upon REB Approval  End date: Dependent on REB Approval |

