Although there are several evidence-based psychotherapeutic treatments for PTSD (e.g., prolonged exposure, cognitive processing therapy [CPT]), drop-out rates are relatively high, not all individuals respond to treatment, impairment persists even after remission of the diagnosis, and the onset of treatment effects is delayed [(1,11,12)](https://www.zotero.org/google-docs/?Evsxy2). To fill these gaps, massed trauma-focused interventions that provide daily treatment over the course of 1-3 weeks have been developed and show promising outcomes, including large effect sizes and high completion rates [(13–16)](https://www.zotero.org/google-docs/?g75eRb). Nonetheless, many do not respond to this delivery strategy and continue to meet criteria for PTSD [(17)](https://www.zotero.org/google-docs/?ODiOxw) and the majority of individuals (80-87%) exhibit residual PTSD and depressive symptoms post-treatment [(18)](https://www.zotero.org/google-docs/?Fyds27). Accordingly, there is a need for novel adaptations of massed PTSD treatment that may help accelerate mechanisms of change and optimize treatment outcomes [(19)](https://www.zotero.org/google-docs/?aITWfR).

Psilocybin is a 5-hydroxytryptaminergic (serotonergic) psychedelic and a non-selective serotonin 2A receptor (5-HT_2AR_) agonist that was first synthesized by Albert Hofmann in 1958 after being originally isolated from psilocybe mushrooms by him in 1957 [(20)](https://www.zotero.org/google-docs/?mpOL4o). Psilocybin was used in psychiatric research from the early to mid-1960s until it was designated a schedule 1 drug in the United States (US) in 1970 [(21,22)](https://www.zotero.org/google-docs/?5qnGXh). Research on the effects of psilocybin resumed in the mid-1990s, and it is currently the preferred compound for use in clinical research of 5-hydroxytryptaminergic psychedelics because it has a shorter duration of action and suffers from less notoriety and stigma than other similar drugs [(23,24)](https://www.zotero.org/google-docs/?q0UCMG). Extant literature investigating the use of psychedelic drugs such as psilocybin focuses on the delivery of these drugs under controlled and optimal conditions in order to produce therapeutic effects. These studies hope to harness the psychospiritual experiences that may be induced by drugs such as psilocybin and direct them into therapeutic experiences for individuals with disorders that may be difficult to treat [(25–28)](https://www.zotero.org/google-docs/?9uyuu9).

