###### **2.6. Study Objectives and Hypotheses**

###### **2.6.1. Primary**

The primary objective of this clinical trial is to evaluate the feasibility and tolerability of psilocybin-assisted CPT in adults with chronic PTSD. Feasibility and tolerability will be determined using recruitment rates, withdrawal, data completion, adherence, number and nature of AEs. **H1**: It is hypothesized that psilocybin and study participation will be generally well tolerated with a 10% study dropout rate.

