###### **3. Method**

###### **3.1. Trial Design**

We propose to conduct an open-label trial in which 15 individuals with PTSD receive 1 week of massed CPT combined with a single dose of psilocybin (25 mg) (Figure 1). Participants will meet criteria for a diagnosis of chronic (i.e., at least six months duration) PTSD with a Clinician-Administered PTSD Scale for DSM-5 (CAPS-5) score of 50 or higher. CPT will be provided remotely twice daily (90 minutes total) over the course of a week. On the third day of the intervention, participants will come in for an in-person (6-8 hour) psilocybin dosing session. Participants will receive a total of 12 CPT sessions, 2 psychotherapy sessions related to psilocybin (preparatory and integration sessions), and one psilocybin dosing session over 7 days. The preparatory session will be completed on day 2 of the treatment week and the integration session will be completed a day after the dosing session (day 4). ​​The primary endpoint of this study will be 1 week after the end of the treatment week (week 2). All study visits including therapy sessions and psilocybin session as well as clinical assessments, will be audio and video recorded, with all recordings preserved for research, training, adherence monitoring and quality assurance purposes. We will measure clinician-assessed PTSD symptoms via Clinician-Administered PTSD Scale for DSM-5 (CAPS-5) global severity scores at baseline, the last treatment day (day 7), and at weeks 5 and 13 (follow-up). Additional outcome measures (i.e., self-reported PTSD symptoms, depression and anxiety severity, psychological function, sleep quality) and measures of putative psychological mechanisms of change (e.g., posttraumatic cognitions, experiential avoidance) will also be measured. Participants will be followed-up weekly from week 2 until week 13 (1 week until 12 weeks post-treatment). Participants will use a commercially available wearable device (Oura Ring) to collect passive data that is relevant to mental health and well-being such as physiological signals, sleep and activity patterns. For more details on the study schedule and administration of scales, please see Table 2.

[figure not shown]

**Figure 1.** Study design with timepoints.

######

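### Section 7.1 presents the pre-post CAPS-5 test as the study's main analysis and credits the change to the treatment, although feasibility is primary and a single open-label arm shows only change from baseline.

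*Protocol*

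**What the plan says.** **What is primary.** The Study Summary gives "Primary outcome: Feasibility" and "Intervention model: Single arm". Section 2.6.1 states: "The primary objective of this clinical trial is to evaluate the feasibility and tolerability of psilocybin-assisted CPT". Section 3.10.1 lists five primary measures: recruitment, withdrawal, data completion, adherence and the percentage of participants with adverse events. CAPS-5 is not among them. Section 2.6.2 places efficacy under the secondary objectives, and Section 3.10.2 names CAPS-5 first among the secondary outcome measures.

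**What Section 7.1 does with it.** The section opens with descriptive feasibility statistics and a confidence-limit rule for judging a full trial feasible. It then describes the before-and-after comparison of PTSD symptoms as the main analysis. Later it says that a Wilcoxon signed rank test of CAPS-5 from baseline to the primary endpoint "will be the main analysis". Between these two statements it says that "this study will primarily detect effects due to psilocybin-assisted CPT on PTSD symptoms", through effect sizes and significance testing.

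**The time point.** Section 3.1 says that the "primary endpoint of this study will be 1 week after the end of the treatment week (week 2" of the follow-up schedule), and Section 7.1 also places the primary endpoint assessment at week 2. Section 3.1 lists the CAPS-5 assessments at baseline, day 7, week 5 and week 13.

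**The concern.** A protocol should give one answer to the question of what the trial is mainly for. Here the objectives and outcome sections give feasibility and tolerability, while the statistics section gives the CAPS-5 change. Someone writing the report from Section 7.1 could lead with a p-value on a secondary outcome and cite the protocol's own labels for doing so.

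The second issue is what that p-value would be taken to mean. The phrase about effects due to the treatment is causal, and the design has no comparator to support it. At stake is what may be concluded from the trial; how it is run is not affected.

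**Working it through.** The protocol states no significance level, effect size or standard deviation for the CAPS-5 test, and Section 7.2 says that no formal sample size calculation was done. There is no figure to reproduce, so the check sets the sections side by side.

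**Step 1: the ranking.**

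| Place in the protocol | Feasibility and tolerability | CAPS-5 or efficacy |
| --- | --- | --- |
| Study Summary | Primary | Secondary |
| 2.6.1 and 2.6.2 | Primary objective | Secondary objective |
| 3.10.1 and 3.10.2 | Five primary measures | Secondary measure |
| 7.1, opening | Confidence-limit rule for a full trial | Not in the rule |
| 7.1, later | Not called the main or primary analysis | Called the main analysis twice; tied to the primary endpoint; said to be what the study primarily detects |

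The last row conflicts with the first three. Nothing in Section 7.1 limits the word *main* to the efficacy objective.

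**Step 2: what the test can show.** The Wilcoxon signed rank test asks whether the paired differences, week 2 minus baseline, are centred on zero. It responds in the same way whatever moved the scores. In this design the candidates are:

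- an effect of the combined treatment;
- natural course, since no untreated group is followed;
- expectancy, since participants know that they receive psilocybin;
- regression to the mean, since entry requires a CAPS-5 score of at least 50 (Sections 3.2.3 and 3.13.2) and the same scale is then tested.

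The last is partly reduced. Selection uses the screening score, taken about four weeks before the first therapy session (3.13.2), while the test starts from a new CAPS-5 taken the day before day 1 (3.13.5). Natural course and expectancy are not addressed in this way. Rejecting the null hypothesis therefore establishes change from baseline and no cause for it.

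**Step 3: the two components.** Every participant receives both massed CPT and psilocybin, so their contributions cannot be separated. The protocol's background says that massed trauma-focused interventions without psilocybin "show promising outcomes, including large effect sizes and high completion rates". It gives no figure there.

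**Step 4: the time point.** Table 2 schedules CAPS-5 at screening, baseline, day 7, week 2, week 5 and week 13. Section 3.1 omits week 2 from its CAPS-5 list, yet the same section names week 2 as the primary endpoint, and Section 7.1 tests CAPS-5 there. On the text of Section 3.1 alone, the data for the named test would not be collected. Table 2 shows that they are meant to be.

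**The case against.** The strongest reply is that this is loose labelling. *Main analysis* may mean the main efficacy analysis, ranked above the outcomes that Section 7.1 assesses for exploratory purposes, and *primary endpoint* is used for a visit rather than a variable. Hypothesis H2 predicts only a decrease, Section 7.1 elsewhere speaks of an effect size associated with the treatment, and the title says open-label. An independent rater administers some of the measures.

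Much of this is fair, and it limits how serious the point is. It does not remove it. The protocol never states the charitable reading, and the sentence about what the study primarily detects concerns the whole study. The softer wording elsewhere shows that Section 7.1 is inconsistent with itself and that suitable language is already available. An independent rater does not replace a control arm.

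Three stronger readings are tempting, and the document does not support them:

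- A reader might infer that the protocol claims an added effect of psilocybin. The sentence attributes change to psilocybin-assisted CPT, which is the combined package. An effect of massed CPT would still be an effect of that package. The inability to separate the components limits interpretation; the sentence does not claim to separate them.
- A reader might infer that a significant CAPS-5 result is nearly assured. That would need an effect size, a standard deviation and a significance level, and the protocol gives none. A power figure would also measure only the test's ability to detect change, which is not the defect.
- A reader might infer that the trial could fail on feasibility and still be declared a success. The rule in Section 7.1 uses only adherence, data completion and withdrawal, and nothing in the protocol defines success by the CAPS-5 p-value. The risk is one of emphasis in reporting.

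**Conclusion.** The concern holds in two parts. First, Section 7.1 ranks the CAPS-5 comparison in a way that contradicts the Study Summary and Sections 2.6.1, 2.6.2, 3.10.1 and 3.10.2. Second, its causal wording claims more than one uncontrolled arm can show, for the combined treatment as well as for psilocybin alone. A related inconsistency is that the CAPS-5 schedule in Section 3.1 omits the week at which the test is made.

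No numerical size attaches to any of this. The conclusion rests on the text and on the single-arm design, with no assumption about effect size or error rate. It affects the wording of two sections and what may be concluded from the result. The sample size, the feasibility rule and the choice of test are untouched.

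**What to change.** In Section 7.1:

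- name the feasibility and tolerability criteria as the primary analysis, and the CAPS-5 Wilcoxon test as the main secondary (efficacy) analysis;
- replace the phrase about detecting effects due to the treatment with *estimate within-person change from baseline after psilocybin-assisted CPT*;
- state that the result does not attribute the change to the treatment or to psilocybin.

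In Sections 3.1 and 7.1, call week 2 the *main efficacy time point* in place of the primary endpoint. In Section 3.1, add week 2 to the listed CAPS-5 assessments so that the text agrees with Table 2.

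The cost is a more modest efficacy claim and a few edited sentences. Sample size, visits and test stay as they are.

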###### **7.2. Sample Size**

Because the anticipated effect size is unknown, a formal sample size calculation cannot be completed. For this trial, it is anticipated that 15 participants will be recruited.

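### The Friedman test named for durability cannot show that benefit over baseline is still present at week 13

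*Protocol*

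**What the plan says.** Protocol section 7.1 lists how long the effect on PTSD symptoms lasts among the things the study will examine. The sentence that sets out the method reads "Durability of effects will be examined by comparing changes from baseline to the assessments at 1 until 12 weeks after the final CPT session", and it continues "for each PTSD subject using Friedman test, which is a non-parametric test method for repeated measures". For the other measures the section adds "Analyses will examine changes from baseline up to week 13 using Friedman tests". Neither sentence says whether baseline is itself a ranked visit, which contrast matters, or what result would count as durable.

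Other statements in 7.1 bear on the point:

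- A Wilcoxon signed rank test of CAPS-5 "scores from the baseline to the primary endpoint will be the main analysis". The primary endpoint is week 2.
- "Baseline will be compared to the primary end point and follow up time points". No test is attached to this sentence.
- "Effect sizes for the psilocybin-assisted CPT will be calculated at the primary endpoint and follow-up time points".
- Means and standard deviations of the scores and of their changes will be reported over the follow-up visits.

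On size, section 7.2 says only that "it is anticipated that 15 participants will be recruited". No standard deviation, correlation or effect size is given. Table 2 schedules CAPS-5 at baseline, Day 7 and weeks 2, 5 and 13. The narrative in section 3.1 omits week 2, but Table 2 marks it.

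**The concern.** Durability asks a directed question against a fixed reference: is the improvement from baseline still there at the end of follow-up? The Friedman null is that the visits entered are exchangeable within a participant. It has no direction and gives baseline no special role. Whichever way the sentence is read, the p-value answers a different question:

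- **Baseline ranked with the follow-up visits.** The null is that no visit differs from any other. A drop at week 2 is enough to reject it, whatever happens later.
- **Changes from baseline ranked.** The null is that the follow-up visits are equal to one another. The distance from baseline plays no part.

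At stake is the durability statement from this trial, which could feed into the larger multi-site trial that section 7.1 contemplates. The primary feasibility objective is not affected.

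**Working it through.** The protocol gives no figure to reproduce, so the check is algebra followed by simulation.

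**Algebra (no assumptions).** Let x(i,j) be participant i's score at visit j and x(i,0) the baseline. The changes are x(i,j) − x(i,0). The same constant is subtracted from every visit of one participant, so the order of that participant's visits does not move. Friedman uses only within-participant ranks: Q = 12/[n·k·(k+1)] × ΣR_j² − 3n(k+1), referred to chi-square with k−1 degrees of freedom, where R_j is the rank sum of visit j. Friedman on changes is therefore identical to Friedman on raw follow-up scores, and baseline has dropped out.

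**Inputs.**

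- n = 15 (section 7.2).
- CAPS-5 at baseline and weeks 2, 5 and 13 (Table 2). So k = 4 with baseline ranked and k = 3 on changes.
- Assumed, because the protocol gives none: normal scores, SD 1 at each visit, equal within-person correlation of 0.3, 0.5 or 0.7, two-sided alpha 0.05.

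**Percentage of simulated trials rejecting, at correlation 0.3/0.5/0.7** (Monte Carlo error about one percentage point):

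| True course in SD (baseline, wk 2, wk 5, wk 13) | Friedman, baseline ranked | Friedman on changes | Wilcoxon, wk 13 v baseline | Wilcoxon, wk 13 v wk 2 |
|---|---|---|---|---|
| No effect (0, 0, 0, 0) | about 5 | about 5 | about 5 | about 5 |
| Kept (0, −1, −1, −1) | 80/92/99 | about 5 | 84/93/99 | about 5 |
| Fully lost (0, −1, −0.5, 0) | 76/90/99 | 64/79/95 | about 5 | 85/93/>99 |

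Down the columns:

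- With baseline ranked, kept and fully lost are indistinguishable.
- On changes, kept and no effect are indistinguishable. Full loss is usually seen.
- The two Wilcoxon columns together give each of the three courses its own pattern.

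**Direction.** On changes, a course that keeps improving (0, −1, −1.5, −2) rejects 64/80/95% of the time, virtually the same as full loss. A rejection alone does not say which has occurred.

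**Partial loss.** If half the benefit is lost (0, −1, −0.75, −0.5), Friedman on changes misses it about 80/72/59% of the time. A direct week-13-against-week-2 Wilcoxon misses the same loss about 68/58/37% of the time. The gain from the directed contrast is 80−68 = 12, 72−58 = 14 and 59−37 = 22 percentage points. The rest of the miss rate comes from having 15 participants.

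**Weekly PCL-5.** With 12 follow-up visits and a linear loss of the whole benefit, Friedman on changes rejects 89/98/100%, so full loss is seen there too.

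**Sensitivity.** With 12 completers (the 20% withdrawal threshold in section 3.10.1: 15 × 0.8 = 12), a 1 SD benefit held to week 5 and gone at week 13 still rejects about 82/93/99% with baseline ranked.

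**The case against.** Four points stand on the other side.

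- **Full loss is not invisible.** A reader might infer that the test cannot tell a lasting effect from a lost one on either reading. The check does not support that. On the literal, changes-only reading, full loss rejects far more often than a kept effect (64/79/95% against about 5%).
- **No decision rule is written.** A reader might infer that a non-significant Friedman result will be reported as durable, so that an ineffective treatment would pass. The protocol says neither. A treatment with no effect would normally also be non-significant in the week-2 Wilcoxon, leaving no effect whose durability could be claimed.
- **Much of the miss rate for partial loss is sample size.** The directed contrast misses half loss often too.
- **Other summaries are planned.** Follow-up changes, effect sizes and baseline comparisons can show whether benefit remains, so the durability statement would not have to rest on a p-value alone. Exact contrasts often sit in an analysis plan, and durability is a secondary matter in a 15-person single-arm feasibility trial.

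These points limit the concern but do not remove it. The protocol has not left the method open: it names the test in the very sentence that says how durability will be examined. The planned summaries are useful, but none is tied to that question.

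**Conclusion.** The point holds in a limited form. The named test cannot show that benefit over baseline remains at week 13. With baseline ranked it rejects almost equally often for a kept and a fully lost benefit (80/92/99% against 76/90/99%). On changes alone it gives a kept effect and no effect the same 5% rejection rate, and a rejection does not separate relapse from further gain. The cancellation of baseline is exact. The percentages depend on the assumed SD, correlations and normal scores, but the pattern holds across correlations of 0.3 to 0.7 and for 12 as well as 15 participants. It does not follow that the trial will misreport durability: no such rule is stated, full loss would usually show on the changes-only reading, and descriptive follow-up results are planned. This should be corrected, but it does not threaten the primary objective.

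**What to change.** In section 7.1:

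1. Make the durability analysis the baseline-to-week-13 CAPS-5 change, with a Wilcoxon signed rank test, the Hodges-Lehmann estimate and its 95% confidence interval.
2. Report beside it the week-2-to-week-13 change with its 95% confidence interval. The baseline contrast alone shows that benefit remains but does not measure how much has been lost.
3. Use the same two contrasts for the other scales, taking Day 7 where week 2 is not collected.
4. Keep Friedman, if wanted, as a descriptive test of any change over time. Say which visits are ranked, and that a non-significant result is not evidence of durability.

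A formal maintenance margin is optional.

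The cost is wording only, since Table 2 already schedules the visits. The downside is wide intervals. On the assumptions above, the SD of a change is √[2(1−ρ)] = 1.18/1.00/0.77. An approximate t-based 95% half-width with 15 participants is 2.145 × SD/√15 = 0.66/0.55/0.43 SD. A claim that benefit was maintained will be hard to make, which is an accurate reflection of what 15 participants can show.
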